**Methods/design:**

One hundred ninety-six patients with T1bN + M0 or T2-4aN0-2 M0 oesophageal squamous cell cancer will be randomised to the DCRT group or the surgery group. In the DCRT group, patients will be given intensity-modulated radiation therapy (IMRT) with 50 Gy/25 fractions and basic chemotherapy with 5-fluorouracil regimens. In the surgery group, patients will receive neoadjuvant chemoradiotherapy (NCRT) and standard oesophagectomy. Five years of follow-up will be scheduled for patients. The primary endpoints are 2-year/5-year overall survival; the secondary endpoints are 2-year/5-year progression-free survival, treatment-related adverse events and the patients’ quality of life. The main evaluation methods include oesophagoscopy, endoscopic ultrasonography and biopsy, oesophageal barium meal, computed tomography, positron emission tomography-computed tomography, blood tests and questionnaires.

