In recent studies, both oxaliplatin and capecitabine have been shown to be at least equivalent to cisplatin and 5-FU in the treatment of advanced upper gastrointestinal (GI) cancer or EC. Also, they can be given as a convenient 2-h infusion and an oral administration, and they have a more favourable toxicity profile compared to cisplatin and 5-FU [15, 16]. Based on these previous findings, this randomised, open-label, multicentre clinical trial aims to compare outcomes in Chinese patients with locally advanced resectable oesophageal squamous cell cancer (ESCC) who have received either NCRT plus surgery or DCRT. The primary endpoints will be 2-year/5-year OS, and the secondary endpoints will be 2-year/5-year progression-free survival (PFS), treatment-related adverse events (AEs) and the patients’ quality of life (QoL). Additionally, in the subgroup analysis of CRT, we will investigate the effect and AEs between the different chemotherapy regimens: Xelox (capecitabine + oxaliplatin), PF (cisplatin + 5-FU) and single capecitabine. This is the first head-to-head clinical trial to compare CRT with radical operation in Chinese mainland people with locally advanced ESCC.

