#### Outcome measures

The primary outcome measures are 2-year/5-year overall survival (OS). The secondary outcomes are 2-year/5-year disease-free survival (DFS), treatment-related AEs and QoL. The recurrence of the disease is defined as either endoscopic recurrence confirmed with biopsy or distant metastasis. The operative mortality is defined as an in-hospital death within 30 days of the perioperative period.

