#### Follow-up

All patients will be followed in the hospital where they received treatment at the 16th week after random allocation and then at 3-month intervals in the first 2 years and at 6-month intervals for the next 3 years thereafter. Local or systemic recurrences and any AEs will be recorded. For the DCRT group, patients can be treated with salvage oesophagectomy if the disease does not reach complete remission at the 16th week follow-up. For the surgery group as well, patients can be treated with radiation or chemotherapy if R0 is impossible to reach or there is local recurrence at the 16th week of follow-up.

QoL will be evaluated in all patients using the Quality of Life Questionnaire-Core 30 (QLQ-C30 version 3.0, in Chinese) and the supplemental Quality of Life-Oesophageal Module 18 Questionnaire (QLQ-ES18, in Chinese) for patients with EC, both of which were developed by the European Organisation for Research and Treatment of Cancer (EORTC). For this evaluation, each patient will be visited in person during hospitalisation 1 week before and 1 week after surgery and contacted by telephone at 12 and 24 weeks postoperatively (Fig. 2) [17].

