Researchers from Hong Kong University initiated an excellent prospective clinical trial to compare the long-term outcomes between DCRT and surgery for ESCC patients. In this study, the overall 5-year survival favours CRT, but the difference did not reach statistical significance (surgery 29.4% and CRT 50%, *p* = 0.147) [13, 14]. The intervention of chemoradiotherapy used in this study is cisplatin 60 mg/m^2^ with hydration therapy given on days 1 and 22, whereas 5-FU is administered as a continuous infusion at 200 mg/m^2^/day from day 1 to day 42. Radiotherapy was delivered as three-dimensional conformal radiation therapy (3DCRT) with a total of 50–60 Gy given in 25–30 fractions over 5–6 weeks. It is inconvenient for patients to be administered 5-FU continuously for 42 days, while IMRT has been reported as more effective and tolerable than 3DCRT. Therefore, we designed this study to investigate the role of DCRT compared with NCRT followed by radical operation in patients with locally advanced ESCC in the highest incidence area worldwide using IMRT (50 Gy/25 F) and different chemotherapy regimens (capecitabine, Xelox, PF, randomised delivery). In the pilot trial, 86 patients finished 16 weeks of follow-up with at least these three regimens in the DCRT group (capecitabine:Xelox:PF = 24:37:25) [19, 20]. The incidences of grade 3–5 AE were 25%, 32.4% and 64% (*p* = 0.03) and the pathological complete response (pCR) rates were 50%, 48.6% and 48% in the three subgroups, respectively (*p* = 0.99). Additionally, objective response rates (ORRs) of 87.5% (21/24), 83.8% (31/37) and 100% (25/25), respectively (*p* = 0.133) were observed. No differences were seen in the complete response (CR) and ORR between the three subgroups. Therefore, it is worth exploring the roles of both the DCRT and single capecitabine in CRT in patients with advanced ESCC using a larger sample size.

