## Abbreviations

3DCRT: Three-dimensional conformal radiation therapy
5-FU: 5-Fluorouracil
AE: Adverse event
CRT: Concurrent chemoradiotherapy
CT: Computed tomography
DCRT: Definitive CRT
EC: Oesophageal cancer
EORTC: European Organisation for Research and Treatment of Cancer
ESCC: Oesophageal squamous cell carcinoma
EUS: Endoscopic ultrasonography
F: Fraction
IMRT: Intensity-modulated radiation therapy
NCRT: Neoadjuvant CRT
OS: Overall survival
PFS: Progression-free survival
QLQ-C30: Quality of Life Questionnaire-Core 30
QLQ-ES18: Quality of Life-Oesophageal Module 18 Questionnaire
QoL: Quality of life

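### The secondary efficacy endpoint is PFS in three places but DFS in the outcome section, and the recurrence definition there has no place for regional or other extraluminal failure

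*Protocol article*

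**What the plan says.** The abstract (Methods/design) says that "the secondary endpoints are 2-year/5-year progression-free survival", together with adverse events and quality of life. The Background repeats this: "the secondary endpoints will be 2-year/5-year progression-free survival (PFS"). The abbreviation list has "PFS: Progression-free survival" and no entry for disease-free survival. The Outcome measures section, where the endpoints are formally set out, says something else: "The secondary outcomes are 2-year/5-year disease-free survival (DFS), treatment-related AEs and QoL".

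That section then defines one component: "The recurrence of the disease is defined as either endoscopic recurrence confirmed with biopsy or distant metastasis". The article gives no list of events for either PFS or DFS.

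The Follow-up section has a wider scope for what is collected: "Local or systemic recurrences and any AEs will be recorded". It also provides for residual disease. In the DCRT group "patients can be treated with salvage oesophagectomy if the disease does not reach complete remission at the 16th week follow-up". In the surgery group, radiation or chemotherapy is allowed if R0 cannot be reached or if there is local recurrence at week 16. It does not say how either situation counts for the secondary endpoint.

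The section on sample size and statistical analysis plans a relative risk with a 95% confidence interval for cancer recurrence, so the recurrence definition feeds an analysis of its own.

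**The concern.** DFS presupposes a point at which the patient is free of disease. PFS does not: a patient with stable or shrinking residual tumour is simply progression-free. In a trial that compares an organ-preserving treatment with resection, the choice of label decides how patients with residual disease are classified. With both labels in print, two reports of the same trial could present different secondary endpoints and each cite the protocol.

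The recurrence definition raises a separate problem. Node-positive disease is eligible, the operation includes a two-field lymphadenectomy, and the radiotherapy target includes malignant nodes. Failure in regional nodes or the mediastinum is therefore foreseeable. Such a failure is neither an endoscopic finding nor a distant metastasis. It could be entered at follow-up as a local recurrence and still fail to meet the definition on which the relative risk for recurrence rests.

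**Working it through.** **1. The endpoint label in each place**

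| Place | Label |
|---|---|
| Abstract, Methods/design | PFS at 2 and 5 years |
| Background | PFS at 2 and 5 years |
| Outcome measures | DFS at 2 and 5 years |
| Abbreviations | PFS only |

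Three places agree and the operative section differs.

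**2. How many patients the label could affect in the DCRT arm**

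The Discussion reports a pilot in 86 DCRT patients (capecitabine 24, Xelox 37, PF 25): "the pathological complete response (pCR) rates were 50%, 48.6% and 48" per cent in the three subgroups. The reported rates are reproduced by whole patients:

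- 12/24 = 50%, 18/37 = 48.6%, 12/25 = 48%.
- Complete responses: 12 + 18 + 12 = 42, and 42/86 = 48.8%.
- Without complete response: 86 − 42 = 44, and 44/86 = 51.2% (exact 95% CI 40.1% to 62.1%).

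The arm size is 96 in the sample size section, or 196/2 = 98 from the total of 196 with 1:1 allocation:

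- 96 × 0.512 = 49 and 98 × 0.512 = 50 patients.
- Over the confidence interval: 96 × 0.401 = 39 to 98 × 0.621 = 61 patients.

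**3. How far the two labels diverge**

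Pilot objective responses were 21 + 31 + 25 = 77. If all 42 complete responders are among them, 77 − 42 = 35 patients responded without complete response, and 35/86 = 40.7%. On response status these patients had not progressed, yet they were not disease-free. For 96 to 98 patients that is 96 × 0.407 = 39 to 98 × 0.407 = 40 whose status depends on the label alone.

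**4. Scope of the recurrence definition**

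| Type of failure | Meets the definition in Outcome measures? |
|---|---|
| Luminal or anastomotic, seen at endoscopy, biopsy-proven | Yes |
| Distant metastasis | Yes |
| Regional nodal or mediastinal | No |
| Other extraluminal locoregional | No |

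The last two rows can fall under the local recurrences recorded at follow-up, so the data collected and the definition analysed do not match.

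**5. What is not touched**

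The sample size rests on 5-year overall survival (29.4% against 50%), α, β and loss to follow-up. None of these inputs depends on PFS or DFS.

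**The case against.** A condensed article commonly leaves event lists, time origins and rules for residual disease to the full protocol or analysis plan, so their absence is no finding. That stands. It does not cover the conflict of labels or the recurrence definition, because there the article states something rather than leaving it out.

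Several stronger readings are tempting, and the article does not support them:

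- **Death is excluded from the endpoint.** A reader might infer this because the definition does not mention death. But the sentence defines recurrence, where death does not belong, and the event list for DFS or PFS is not printed.
- **The endpoint is undefined for half the DCRT arm.** This holds only under a DFS reading and only if the pilot rate carries over. Under PFS from randomisation these patients can be classified. Salvage oesophagectomy may also make some of them disease-free, and nothing in the article sets week 16 as the DFS origin.
- **The definition favours surgery.** Only the DCRT arm keeps the whole oesophagus, so unequal counting is plausible. But the definition is worded identically for both arms, an anastomotic recurrence can be proven at endoscopy after surgery, and nodal failure is uncounted after DCRT too. There are no failure-pattern data from which to judge direction or size.
- **Randomisation will be broken by comparing responders with R0 patients.** No such analysis is proposed.

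Finally, this is a secondary endpoint for which the article states no power calculation, which limits the severity.

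**Conclusion.** The point holds in two parts. First, the article names two different secondary efficacy endpoints, and they classify residual disease differently in a design that expects residual disease. Second, the recurrence definition, followed as written, does not count regional nodal, mediastinal or other extraluminal failure, although local recurrences are to be recorded and a relative risk for recurrence is planned.

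The size under a DFS reading is about half the DCRT arm: 49 to 50 patients, or 39 to 61 over the confidence interval. This assumes that the pilot rate applies to this trial and that the pilot figure, labelled pathological complete response and then discussed as complete response, is a fair proxy for complete remission at week 16. It counts patients whose status is unclear; it does not measure bias. The number of failures that the recurrence definition would miss cannot be derived from the article.

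This should be fixed. Overall survival as primary endpoint and the sample size stand as they are.

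**What to change.** In Outcome measures:

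1. Replace DFS by PFS at 2 and 5 years, to match the abstract, the Background and the abbreviation list.
2. Widen the definition of recurrence or progression to include regional nodal and other extraluminal locoregional failure shown by imaging or biopsy, alongside biopsy-confirmed endoscopic recurrence and distant metastasis. Use the same definition for the relative risk of recurrence.
3. State that PFS runs, in both arms and in all randomised patients, from randomisation to the first progression or recurrence at any site or death. The only time origin now printed is initial diagnosis, for the Kaplan-Meier curves, so the origin for PFS needs to be stated explicitly.

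The cost is a change of wording and of event coding, best made before outcome data are analysed. The abstract lists CT, PET-CT and endoscopy among the evaluation methods, but the schedule figure is not available here. The sponsor should therefore confirm that the planned follow-up imaging is enough to detect regional failure in both arms. No change to the sample size is needed.

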## Background

Oesophageal cancer (EC) is the eighth most common cancer worldwide and the sixth leading cause of cancer-related death [1]. In 2012, 456,000 EC cases occurred, and 400,000 people died from EC worldwide. It’s remarkable that almost half of them came from China, with 223,000 EC cases and 197,000 death cases in 2012. Both the highest incidence and highest mortality, 379/100,000 and 150/100,000, respectively, were in Henan, China (including Linzhou, Anyang and Huixian cities). Additionally, EC is the fourth most deadly cancer among men in China; it is responsible for 9.8% of all cancer deaths annually [2].

Worldwide, approximately half of these patients present with locally advanced disease [3]. Radical oesophagectomy remains the most popular treatment for this disease, but the long-term survival is still barely satisfactory [4, 5]. The mortality in the perioperative period is approximately 5% at renowned centres. The 5-year survival rate in patients with oesophageal carcinoma treated by surgery alone is just 10–20% [6]. Numerous clinical studies in past decades have used adjuvant or neoadjuvant chemotherapy and radiotherapy as a tool to improve the clinical outcome of surgery [7]. However, the results from prospective randomised trials on neoadjuvant radiotherapy or chemotherapy alone were not satisfactory [8]. There was no survival benefit associated with these approaches [9].

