### Sample size estimation and statistical analysis

Sample size calculation is based on the 5-year OS rates: 29.4% in patients treated with oesophagectomy and 50% in the DCRT group [18]. We used the log-rank test to compare the survival rate difference between the surgery and DCRT group. We defined α as 0.05 and β as 0.2. We supposed that the rate of loss to follow-up per year is 2.5% and 12.5% in 5 years. A sample size of 96 patients was determined to be required for each group.

The primary and secondary outcome measures will be compared using Student’s *t* test for the normally distributed data and the Mann-Whitney *U* test for the nonparametric data. For the data in proportions, a chi-squared test or Fisher’s exact test (if one of the expected values is less than 5) will be used. The provision of a 95% confidence interval will be calculated with the relative risk for cancer recurrence, morbidities and mortalities related to each therapy. We will use the Kaplan-Meier curve to represent the probability of survival within 2 years and 5 years after the initial diagnosis, and compare the two groups using the log-rank test. A value of *p* < 0.05 is considered to be statistically significant. The statistical analysis will be performed with the SPSS software (version 13.0; SPSS Inc., Chicago, IL, USA).

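### Operative mortality counts only in-hospital deaths within a 30-day window with no fixed start, so surgical mortality can be understated (minor; cheap to correct)

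*Protocol article*

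**What the plan says.** The Outcome measures section of the protocol article gives one definition of a mortality measure other than overall survival: "The operative mortality is defined as an in-hospital death within 30 days of the perioperative period". Operative mortality is not itself among the listed outcomes. The primary outcome is overall survival at 2 and 5 years, and for the rest the section says: "The secondary outcomes are 2-year/5-year disease-free survival (DFS), treatment-related AEs and QoL".

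The section on sample size and statistical analysis plans a 95% confidence interval with the "relative risk for cancer recurrence, morbidities and mortalities related to each therapy". It does not say which deaths count as related to a therapy, and it does not mention operative mortality.

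Two other places bear on the point. The Background says: "The mortality in the perioperative period is approximately 5% at renowned centres". The Follow-up section allows surgery in the definitive chemoradiotherapy (DCRT) arm too: "patients can be treated with salvage oesophagectomy if the disease does not reach complete remission at the 16th week follow-up".

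**The concern.** The definition joins two conditions, place and time, and a death must meet both. A death after discharge fails the first condition however soon it follows the operation. The time condition is also loose: the perioperative period is an interval, and the text does not say whether the 30 days start at its beginning, at the operation or at its end.

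This is not a detail left to a fuller document. The article states a rule, and the rule as stated leaves out deaths that a reader would expect a 30-day operative mortality to include. Early mortality is one of the figures by which readers will judge a surgical strategy against a non-surgical one, so the count should not depend on whether the patient had gone home.

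The definition is also unsuitable for comparing the arms. It takes in only deaths linked to an operation. It therefore omits deaths during neoadjuvant chemoradiotherapy, which is part of the surgery arm's strategy, and in the DCRT arm it could apply only to salvage oesophagectomy.

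**Working it through.** **Figure to reproduce.** The article states no expected operative mortality for this trial and no expected relative risk, so there is none. The sample size enters below only as a denominator: 96 per group as stated in the sample-size section, or 196/2 = 98 from the total in the Patients section.

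**Step 1: apply the rule to example deaths.**

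| Death in the surgery arm | In hospital? | Within 30 days? | Counted? |
|---|---|---|---|
| In hospital, day 20 after surgery | yes | yes | yes |
| At home, day 20 after surgery | no | yes | no |
| Same admission, day 35 after surgery | yes | depends on where the 30 days start | unclear |
| During neoadjuvant chemoradiotherapy, before surgery | either | no operation yet | no, on the ordinary meaning of operative |

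The second row follows directly from the wording. The third does not: day 35 is outside the window if the clock starts at the operation, but may be inside it if the clock starts at the end of the perioperative period.

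**Step 2: direction.** Take in-hospital to mean the surgical admission. Every postoperative death that the stated rule counts, on either reading of the clock, is then also counted by a rule of death within 30 days of surgery anywhere, or at any time in the same admission. The reverse is not true. The difference can only go one way, towards a lower reported figure.

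**Step 3: size, as an illustration.** Inputs: 5% from the Background, and an assumed share *s* of these deaths that falls outside the rule. The documents give no value for *s*.

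Deaths counted = n × 0.05 × (1 − s); rate reported = 0.05 × (1 − s).

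| s (assumed) | n = 96: counted | n = 98: counted | Rate reported | Deaths left out |
|---|---|---|---|---|
| 0% | 4.8 | 4.9 | 5% | 0 |
| 20% | 3.84 | 3.92 | 4% | about 1 |
| 40% | 2.88 | 2.94 | 3% | about 2 |

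**Step 4: the relative risk, only if operative mortality were used as its surgery-arm numerator.** Assume 2 fully counted deaths of 96 in the DCRT arm (about 2%; not in the documents). RR = a/b with n = 96 per arm, SE(ln RR) = √(1/a − 1/n + 1/b − 1/n), and 95% limits RR × exp(±1.96 × SE).

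- 5 v 2: SE = √(0.2 − 0.0104 + 0.5 − 0.0104) = 0.824; RR 2.5, about 0.5 to 12.6.
- 4 v 2: RR 2.0, about 0.4 to 10.7.
- 3 v 2: RR 1.5, about 0.3 to 8.8.

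The point estimate would move noticeably, but every interval is wide and includes 1. One or two reclassified deaths would not change a conclusion.

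**The case against.** A reader might infer that the between-arm mortality comparison is already not like with like. The article does not support that. The planned relative risk concerns deaths related to each therapy, a broader term, and nothing says that the in-hospital 30-day count is its surgery-arm numerator. A definition and window for therapy-related death may well stand in the full protocol or analysis plan, so their absence from a journal article is not a fault. An operative-mortality definition naturally covers only operated patients, and having no DCRT counterpart is not an error in it.

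A reader might also infer that these deaths are lost to the trial. They are not. All of them enter overall survival. Treatment-related adverse events are a secondary outcome, and the Monitoring section has all serious events recorded and each followed up, with causality considered.

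The magnitude is open to challenge as well. The 5% is a background figure whose own counting rule is not given; if it already rests on a restricted rule, the illustration does not apply. It also supposes that every patient randomised to the surgery arm is operated on.

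Finally, counting all deaths from randomisation measures early all-cause mortality, a different quantity from therapy-related mortality and one that the survival curves partly show.

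All of this limits the point to a safety measure that is not a listed outcome. None of it answers the plain reading of the definition, which leaves out a death at home within 30 days and does not fix when the 30 days begin.

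**Conclusion.** The point holds as a defect of definition. The stated rule excludes deaths after discharge within 30 days and has no fixed start, so reported surgical mortality can be understated but not overstated relative to a full count. That direction rests on in-hospital meaning the surgical admission.

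The size cannot be derived from the documents. The illustration of 3% to 4% reported in place of 5%, about 1 to 2 deaths, rests on an assumed 20% to 40% share, on the 5% being a full count, and on all 96 to 98 surgery-arm patients being operated on.

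A distorted relative risk between the arms is only conditional: it would arise if the operative-mortality count were used as the surgery-arm numerator, which the article does not say. The primary comparison is unaffected. Severity: minor; a cheap improvement.

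**What to change.** Define operative mortality as death from any cause within 30 days of the date of surgery, in or out of hospital, or at any time in the same admission. State whether salvage operations in the DCRT arm are reported under the same definition.

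If the planned relative risk for therapy-related mortality is meant to compare the arms on early death, do not use the operative count for the surgery arm. Count deaths in both arms from randomisation over one common window, regardless of place, so that deaths during neoadjuvant chemoradiotherapy are included, and label the result early all-cause mortality. The window should be long enough to cover 30 days after the planned operation. The article does not give the interval between neoadjuvant treatment and surgery, so the sponsor must set the length.

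Make the change before deaths are tabulated by arm, so that the rule is not chosen with the results in view. The cost is small: dates of death are already needed for overall survival, and only the dates of surgery and discharge are needed in addition. The downside is that reported surgical mortality may be slightly less favourable.
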